#### D.11.5. Outcome ascertainment

Outcomes will be determined by review by the **Clinical End Point Committee**. This panel will be blinded to the intervention group. The primary outcome is reported in section D3. The Clinical End Point Committee will ascertain cardiovascular deaths from clinical registers on the basis of the clinical records and a death certificates listing an International Classification of Diseases code corresponding to any cardiovascular death (CHD or stroke). A definite non-fatal MI refers to a report of a clinical MI by a clinical center that meets the criteria for MI described in the Manual of Operations. Myocardial infarction is defined by the presence of symptoms suggestive of ischemia or infarction, with either EKG evidence (new Q waves in two or more leads) or cardiac-marker evidence of infarction, according to the standard American College of Cardiology definition (**Cannon, 2001**). Stroke diagnosis is based on rapid onset of a neurological deficit lasting more than 24 hours, supported by imaging studies (CT or MR scans). Secondary analyses will also be done.

#### D.12. Statistical Analyses

The analyses will be based on the intention-to treat principle. With the actual sample size, it is assumed that we will have enough statistical power to evaluate the effects of the MeDiet (the two MeDiet groups considered as a single one) compared to the Low-fat Control diet on the primary prevention of cardiovascular diseases. We also might be able to assess differences in outcomes for the two MeDiets if the specific supplements of EVOO and mixed nuts prove to be differentially cardioprotective. The main variable for analysis will be time from randomization to event. For a given outcome, the time of the event will be defined as the number of days from randomization to the first post-randomization diagnosis, as determined by the adjudicator. For silent MI, the date of the follow-up EKG will be applied. Participants without a diagnosis will be censored at the time of last follow-up contact. The generally accepted method for analyzing this type of data is the log rank statistic. It has the advantage of requiring no assumptions other than the random assignment of the intervention. This analysis will be the primary measure of the success or failure of the trial. However, if baseline imbalances between groups are observed for any of the main CHD risk factors, a Cox proportional hazard analysis will be conducted stratified by FC, age, sex and adjusted for major risk factors. Primary outcome comparisons will be estimated as hazard ratios. Adjustment for other relevant variables (body mass index, physical activity, education level, marital status) also will be applied.

#### D.13. Monitoring Plan

The Data and Knowledge Management Center (DKMC) will be responsible for preparing reports to monitor the progress of the study for the Steering Committee and the Data and Safety Monitoring Board (DSMB). These reports will focus on a) general progress of candidate recruitment and person-year of follow-up in comparison to pre-established targets; b) participant adherence (biochemical markers and FFQ data of compliance and comparison with targets for nutrients and food groups); c) quality control (digit preference, variability, outliers); d) clinical outcome data at each center and primary and secondary endpoints (group comparisons with respect to both the primary outcome, total mortality, and other secondary outcomes). In these sections, data will be provided for the study as a whole and, where appropriate, separately for each FC. Reports will be

mailed to members of the DSMB two weeks prior to the meeting or to the date of review. Steps will be taken to insure security and confidentiality, including distribution by certified mail and enactment of a return policy of all reports. Comparison of groups with respect to major outcomes will be updated two days before the meeting so that the DSMB will have the most up-to-date data possible.

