### D.14. Organizational structure

An overview of the organizational structure is displayed in <http://www.predimed.org>. The main funding for the trial comes from ISCIII (Spanish Government). A **Data and Safety Monitoring Board** (DSMB) supervises the trial. The Project Leader, [name] (Hospital Clinic, University of Barcelona), is assisted by the **Steering Committee** to make strategic decisions along the project's life. The coordination, research and internal supervision activities of the project will be performed by the following three categories of units: coordination units, research and operative units, and subcommittees. Table 3 shows data of each unit. In summary, the research team includes 10 **Field Centers** (FC), three **Data Management and Statistical Units** (DMSU); a **Data and Knowledge Management Center** (DKMC); and 6 **Specialized Laboratory Units** (SLU). The **Steering Committee**, chaired by [name], includes the coordinators of each of the 11 FC, the investigator responsible of the each SLU and the Data Manager. There are also the following organizational structures: a **Diet Subcommittee**, co-chaired by [name] (Navarra) and [name] (Barcelona), a **Measurement Subcommittee**, chaired by [name] IMIM-Barcelona), a **Recruitment Subcommittee** (chaired by [name]), a **Clinical End Point Committee**, chaired by [name] (Cardiologist, Txagorritxu Hospital, Vitoria) and will include a clinician from each FC. The DSMB includes the following external advisors: [name], Harvard School of Public Health, Boston; [name], Columbia

University College of Physicians and Surgeons, New York; [name], Loma Linda University, CA; [name], Principal Investigator of the Spanish branch of the EPIC Study, Barcelona. They will convene to review the implementation of the protocol and to monitor the trial's progress on an annual basis. In addition, as stated, a mailed report will be sent them periodically with the pertinent analyses to ascertain the continuation of the PREDIMED trial. Most of the Committees will convene by conference calls and at in-person meetings (twice per year during years 1-4, once during year 5). The frequency of contacts will vary during the trial.

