|                               | Zaragoza University                                | SLU-5                                                                                                                                                      |
|                               | Barcelona University – Pharmacy School             | SLU-6                                                                                                                                                      |

\*CSIC: Superior Council for Scientific Research. IMIM: Municipal Institute for Medical Research.

A private web-based system of data access has been created ([www.predimed.org](http://www.predimed.org)), where authorized investigators can download all the forms, datasets and published papers.

For privacy and security, an ID and password are required to access the data and the forms. This web-based system is used to send data to the Data Manager. Quality control reports will be generated for key aspects of the trial, i.e., digit preference and variability. To reduce data entry expenses and speed processing, the questionnaires and data forms are optically scannable. The data forms will be entered in duplicate and missing data checks will be performed. After data entry, cross-form edit checks will also be performed. Data inconsistencies will be checked. Audits will be rerun periodically to detect unsolved problems. Standardized edit reports that summarize problems in the database provide an additional method of assuring data quality. To minimize the potential for error, we have developed a detailed Manual of Operations. In addition we will conduct annual training meetings for staff. The DKMC will monitor the performance of each FC and will recommend new or corrective procedures in case deficiencies are noted. Until the end of the trial, all FC will be masked to trial outcome data, with the exception of the statisticians, the Data Manager and the external DSMB. Due to the nature of the intervention, however, dietitians and nurses at each FC need to be unmasked to diet assignment. The Clinical Event Subcommittee will be blinded to participants' allocation.

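### As written, D.13 gives the Steering Committee, which includes every field-centre coordinator, outcome comparisons by arm, contradicting the masking rule in D.15

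*Supplement*

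**What the plan says.** All references are to protocol Version 2 (May 2009).

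- **D.13, recipients.** The reporting task falls to the DKMC, the trial's Data and Knowledge Management Center. This unit "will be responsible for preparing reports to monitor the progress of the study for the Steering Committee and the Data and Safety Monitoring Board".
- **D.13, content.** The next sentence lists items a) to d) for these reports and does not divide them by recipient. Item d) covers outcome data at each centre and "primary and secondary endpoints (group comparisons with respect to both the primary outcome, total mortality, and other secondary outcomes".
- **D.13, level of detail.** "In these sections, data will be provided for the study as a whole and, where appropriate, separately for each FC".
- **D.13, delivery.** Reports are "mailed to members of the DSMB two weeks prior to the meeting or to the date of review", by certified mail and under a return policy. No delivery to the Steering Committee is described.
- **D.14, membership.** The Steering Committee "includes the coordinators of each of the 11 FC, the investigator responsible of the each SLU and the Data Manager".
- **D.15, masking.** "Until the end of the trial, all FC will be masked to trial outcome data, with the exception of the statisticians, the Data Manager". The third party exempted is the external DSMB. D.15 also says that dietitians and nurses know the diet assignment and that the event committee does not.

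**The concern.** Interim results by arm are normally confined to the monitoring board and the statisticians who serve it. Here the monitoring section names the trial's own strategic body as a recipient of the same report, and that body contains the people who run the field centres.

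The matter carries weight in this trial for four reasons.

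- Delivery staff are unmasked (D.15), and D.9 describes feedback between dietitians and centre coordinators. Knowledge of an interim trend could alter how hard each diet is promoted.
- Adjudication is blinded (D.11.5), which protects the classification of events. A non-fatal infarction, however, first has to be reported by a clinical centre, and blinding the committee does not protect that step.
- Participants without an event are censored at their last contact (D.12). Unequal effort to retain participants could therefore reach the primary log-rank comparison.
- The Steering Committee helps make strategic decisions (D.14), and the amendment list shows that it has changed the protocol during the trial: in October 2006 it altered the intensity of the control intervention. That change is not criticised here. It shows only that what this committee knows can bear on the design.

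**Working it through.** No arithmetic applies, because the point does not depend on alpha, power, event rates or sample size. The check sets the current sections side by side.

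1. **Who receives the reports?** D.13 names two recipients in one sentence, the Steering Committee and the DSMB.
2. **What do the reports contain?** D.13 gives a single list for both. Item d) includes between-group comparisons on the primary outcome, mortality and the other secondary outcomes, for the whole study and where appropriate by centre. No sentence in Version 2 limits item d) to the DSMB.
3. **Who sits on the Steering Committee?** Under D.14, the coordinators of all field centres, the heads of the laboratory units and the Data Manager. D.14 gives the number of field centres as 10 in one sentence and 11 in another. The point is the same with either number.
4. **Who may see outcome data?** D.15 masks all field centres until the end of the trial. It exempts three parties: the statisticians, the Data Manager and the external DSMB. Neither the Steering Committee nor the coordinators are exempt.
5. **Can all of these hold?** By steps 1 to 3, each coordinator belongs to a body for which the comparisons are prepared. By step 4, each coordinator must not see them. Both cannot be followed as written.
6. **Does the delivery text resolve it?** Only in part. The mailing rules concern DSMB members, and the late update is likewise for them: "Comparison of groups with respect to major outcomes will be updated two days before the meeting so that the DSMB will have" current data. This suggests where the comparisons were meant to go. It does not remove the other named recipient or narrow the content of the shared report.
7. **The Data Manager.** This person co-directs the DKMC, which prepares the reports (D.15 and D.13), is exempt from masking (D.15), sits on the Steering Committee (D.14) and exchanges feedback with centre coordinators (D.9). Because the exemption is explicit, this is no contradiction. But no sentence says that results by arm must not pass from this role to the committee.

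The period at issue covers the formal interim analyses at 2, 3, 4 and 5 years of median follow-up (D.13.2), with closeout by 31 December 2011 (D.5.5).

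**The case against.** The strongest reply is that D.13 is condensed drafting and not a decision to unmask anyone. Every concrete delivery detail concerns the DSMB, D.15 states the masking rule in force, and D.13 can be read within that limit. Version 1 kept two separate report lists and excluded endpoints from the Steering Committee's. None of the listed amendments mentions a change of policy. The event committee is blinded, the stopping boundaries are fixed p-values, and the recommendation to stop or continue belongs to the DSMB (D.13.2).

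Much of this stands. A reader might infer that group comparisons are in fact sent to the Steering Committee, or that the masking in D.15 does not exist. The documents support neither: no such delivery is described, and D.15 is current text. A reader might also suppose that coordinators direct the dietitians and nurses, but D.9 speaks only of feedback and discussion. Nor do the documents show that the group-sequential boundaries themselves are compromised.

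What the reply does not do is supply the missing sentence. Likely intent, inferred from a superseded version, does not govern how the current section is carried out. Staff who follow D.13 literally would give coordinators what D.15 forbids.

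**Conclusion.** D.13, read with D.14, contradicts D.15 on whether field-centre coordinators may see outcome comparisons by arm. The finding is an internal inconsistency in the current protocol, and it rests on the plain wording of the three sections.

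Its size cannot be expressed as a bias. No unblinding is shown, and Version 2 gives neither a schedule nor a delivery route for Steering Committee reports. The potential exposure, assuming D.13 were followed literally, is the coordinators of up to 11 centres plus the laboratory heads, for as long as follow-up continues. It should be corrected before the next report is prepared, because knowledge of an interim difference cannot be withdrawn once given.

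**What to change.** Split the reports in D.13.

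- **Steering Committee report:** recruitment, person-years, adherence, data quality, and outcome data pooled over arms only. State that it contains no endpoint by arm.
- **Closed report:** the group comparisons on the primary outcome, mortality and secondary outcomes, for the DSMB only, prepared by staff already unmasked under D.15. The existing rules on certified mail, return of copies and the late update then apply to this report.
- **Data Manager:** add a sentence that arm-level outcome results are not to be disclosed to the Steering Committee, because this role is both unmasked and a member. Removing the Data Manager's access or committee seat is not needed for the fix. Removing access could mean reorganizing the unit that prepares the reports.
- **D.15:** say that the masking of field centres concerns outcome results by arm, so that pooled outcome data in the Steering Committee report do not reopen the conflict.

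The cost is a few sentences in D.13 to D.15 and a second report template. The interventions, sample size, stopping boundaries and analysis stay as they are.

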#### D.13.1. Quality of Data

To assess the reliability of the data included in the questionnaires and databases, external personnel will review medical records of a random sample of the participants. Data of around 25% of the participants included in each FC will be evaluated. Then DKMC and Data and Knowledge Management Center (DKMC) members will confirm these data (See later).

#### D.13.2. Data analysis

The data from the PREDIMED trial will be analyzed at 5 intervals (4 interim analyses and the final analysis). The 4 interim analyses to decide on the continuation of the PREDIMED trial will be conducted after 2, 3, 4 and 5 years of median follow-up. The 2-sided p-values for stopping the trial at each interim analysis (1st to 4th) are respectively  $5 \times 10^{-6}$ , 0.001, 0.009 and 0.02 for benefit, and  $9 \times 10^{-5}$ , 0.005, 0.02 and 0.05 for adverse effects, according to asymmetric O'Brien-Fleming boundaries (**O'Brien, 1979**). The actual recommendation regarding stopping or continuing the trial will be made by the DSMB. There are 3 potential reasons for early ending of the trial: a) efficacy of MeDiet may be demonstrated; b) harmful effects of the intervention may be discovered; c) there may be no hope for a reasonable evaluation of the proposed hypothesis (i.e., if a small intervention differential exists, power may be seriously compromised and early termination of the trial may be considered). Early termination should be considered only if the intervention effect is really great.

### D.14. Organizational structure

An overview of the organizational structure is displayed in <http://www.predimed.org>. The main funding for the trial comes from ISCIII (Spanish Government). A **Data and Safety Monitoring Board** (DSMB) supervises the trial. The Project Leader, [name] (Hospital Clinic, University of Barcelona), is assisted by the **Steering Committee** to make strategic decisions along the project's life. The coordination, research and internal supervision activities of the project will be performed by the following three categories of units: coordination units, research and operative units, and subcommittees. Table 3 shows data of each unit. In summary, the research team includes 10 **Field Centers** (FC), three **Data Management and Statistical Units** (DMSU); a **Data and Knowledge Management Center** (DKMC); and 6 **Specialized Laboratory Units** (SLU). The **Steering Committee**, chaired by [name], includes the coordinators of each of the 11 FC, the investigator responsible of the each SLU and the Data Manager. There are also the following organizational structures: a **Diet Subcommittee**, co-chaired by [name] (Navarra) and [name] (Barcelona), a **Measurement Subcommittee**, chaired by [name] IMIM-Barcelona), a **Recruitment Subcommittee** (chaired by [name]), a **Clinical End Point Committee**, chaired by [name] (Cardiologist, Txagorritxu Hospital, Vitoria) and will include a clinician from each FC. The DSMB includes the following external advisors: [name], Harvard School of Public Health, Boston; [name], Columbia

University College of Physicians and Surgeons, New York; [name], Loma Linda University, CA; [name], Principal Investigator of the Spanish branch of the EPIC Study, Barcelona. They will convene to review the implementation of the protocol and to monitor the trial's progress on an annual basis. In addition, as stated, a mailed report will be sent them periodically with the pertinent analyses to ascertain the continuation of the PREDIMED trial. Most of the Committees will convene by conference calls and at in-person meetings (twice per year during years 1-4, once during year 5). The frequency of contacts will vary during the trial.

### **D.15. Data management**

The DKMC will be co-directed by the Data Manager, [name], and [name]. With the support of the DMSUs (IMIM, Navarra University & Hospital Clinic-Barcelona), they will develop and maintain the data base; and will provide statistical and trial monitoring support throughout the fieldwork. Data from screening, intervention and follow-up visits will be entered on specific forms at the FC, and sent monthly to the Data Manager in the DKMC, who will send reports of missing or inappropriate entries, for clarification and resolution, to the FC coordinators every month. The Data Manager will also provide monthly reports to [name] on the quality and completeness of the data, organized by type of visit (screening visit 1, 1-year follow-up visit, etc.) and by specific data form. At the end of each yearly visit in each FC, the Data Manager will verify the completeness of data for each individual.

|                               | Zaragoza University                                | SLU-5                                                                                                                                                      |
|                               | Barcelona University – Pharmacy School             | SLU-6                                                                                                                                                      |

\*CSIC: Superior Council for Scientific Research. IMIM: Municipal Institute for Medical Research.

A private web-based system of data access has been created ([www.predimed.org](http://www.predimed.org)), where authorized investigators can download all the forms, datasets and published papers.

For privacy and security, an ID and password are required to access the data and the forms. This web-based system is used to send data to the Data Manager. Quality control reports will be generated for key aspects of the trial, i.e., digit preference and variability. To reduce data entry expenses and speed processing, the questionnaires and data forms are optically scannable. The data forms will be entered in duplicate and missing data checks will be performed. After data entry, cross-form edit checks will also be performed. Data inconsistencies will be checked. Audits will be rerun periodically to detect unsolved problems. Standardized edit reports that summarize problems in the database provide an additional method of assuring data quality. To minimize the potential for error, we have developed a detailed Manual of Operations. In addition we will conduct annual training meetings for staff. The DKMC will monitor the performance of each FC and will recommend new or corrective procedures in case deficiencies are noted. Until the end of the trial, all FC will be masked to trial outcome data, with the exception of the statisticians, the Data Manager and the external DSMB. Due to the nature of the intervention, however, dietitians and nurses at each FC need to be unmasked to diet assignment. The Clinical Event Subcommittee will be blinded to participants' allocation.

#### **D.16. Limitations of the study**

Fat consumption is customarily high in Mediterranean countries. Due to this fact, some participants have difficulty in following a low-fat diet on the long-term. We acknowledge this limitation because participants in the low-fat diet control group belong to a Mediterranean culture and their food habits are derived from the fat-rich traditional MeDiet (**Serra-Majem, 2007**). We believe that it would be unethical to strongly advise participants assigned to the control diet group to abandon this supposedly healthy diet. Instead, we are attempting to increase differences by using a comprehensive and expanded intervention in both experimental groups to attain further changes in their diet, thus maximizing the contrast.

The main differential point in our design is that we are evaluating two MeDiets that are higher in fat than all diets assessed by previous trials, but in both of them the main sources of fat are unsaturated fatty acids. In addition, the effects of diets rich in polyphenols and phytosterols are also assessed. The rigorous methodology of the PREDIMED trial should convincingly answer what is certainly one of the major sources of controversy and unresolved issues regarding diet and cardiovascular risk, namely, the impact of replacing saturated fat with MUFA or with carbohydrate.

